#### Decision aid

The development of the decision aid was based on a framework suggested by Coulter et al. [31], in accordance with the IPDASi (the International Patient Decision Aid Standards instrument) criteria [32]. The process comprised six steps: (1) defining the purpose of the decision aid and the target population, i.e. decision about CRC screening uptake in lower educational attainment citizens; (2) formation of steering group, comprising both screening experts and experts on shared decision making (no citizens were included in the steering group); (3) designing the decision aid, based on Danish lower educational attainment citizens’ information needs, as described in a previous study [25]; (4) alpha testing the decision aid to check usability and design – this step included both lower educational attainment citizens and healthcare professionals and used both focus group interviews and e-mail correspondence; (5) external peer reviewing also included citizens and healthcare professionals; and (6) the beta or user-testing with lower educational attainment citizens assessed feasibility, comprehensibility, and usability. Based on inputs from all steps, the final decision aid was completed by a professional web design agency, supervised by the steering group [26].

The decision aid is an online tool. The online design was chosen, since digital communication is mandatory in Denmark, and 91.3% of the population (aged 45–74 years) has access to digital mail [28]. Further, the online design opens up possibilities to feature more advanced functions, e.g. questions for the participant during the process, and a summary of answers at the end, presented as a “choice indicator.” The decision aid consists of 15 steps in total. Each step presents facts in a figure or chart and, via links in these, pop-ups with further information are available. The figures used are icons (e.g. illustrating colon with a polyp and cancer), pie charts, crowd-figures, and a flow chart illustrating the possible steps in CRC screening. Almost all pop-ups have a “read more” function. The decision aid is available in Danish by contacting the authors.

### Study population

Two samples of citizens will be provided by the Danish Health Data Authority from the Danish Civil Registration System [33]: (1) a random sample of 10,000 53–74-year-old citizens, born in December, and resident in the Central Denmark region on 1 August 2017 (expected to be invited for screening during October–December 2017); and (2) a random sample of 5000 50–74-year-old citizens, born in October, and resident in the Central Denmark Region on 1 August 2017 (invited for screening during January–March 2017) for the historic study arm (Fig. 1). The lists will contain civil registration number, name, and postal address of the sampled citizens. No incentives are used in this trial.

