**Methods:**

The LEAD (Lower Educational Attainment Decision aid) trial will be conducted as a two-arm randomized controlled trial among 10,000 50–74-year-old citizens, resident in the Central Denmark Region not yet invited to take up colorectal cancer screening. Citizens will receive a baseline questionnaire. Respondents will be allocated into the intervention or the control groups. Citizens in the intervention group will receive the decision aid whereas the control group will not. Those who return a stool sample within 45 days after receiving the screening invitation and those with medium or higher educational attainment are excluded. Both groups will receive a follow-up questionnaire 90 days after being invited to colorectal cancer screening.

A historic cohort consisting of 5000 50–74-year-old citizens resident in the Central Denmark Region, having received their screening invitation in the beginning of 2017 will be included. This cohort will receive a follow-up questionnaire 6–9 months after they received the screening invitation.

Informed choice will be evaluated by assessing levels of knowledge, attitudes, and screening uptake. Analyses will be conducted as intention-to-treat analyses. Additionally, differences between levels of worry and decisional conflict between groups will be assessed as secondary outcomes.

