## Methods

### Setting

CRC screening with biennial FIT was introduced in Denmark in 2014 with an initial “prevalence round” of invitations for four years, where all citizens aged 50–74 years are invited once, according to month of birth. Citizens turning 50 or 75 years during the prevalence round are invited just before their birthday if not invited earlier. From 2018, all citizens in the target group will receive biennial invitations (identifying incident CRC). The screening program is locally administered in five regions. This study is carried out in the Central Denmark Region, which is the second largest region with roughly 395,000 citizens aged 50–74 years [27].

In the CRC screening program, the mailed screening invitation contains a screening kit (collection tube and collection paper), instructions on how to obtain the sample, an official information leaflet, and a pre-stamped, pre-addressed envelope. If a screening sample is not returned within 45 days, a digital reminder is sent (see below). Test results are digitally mailed to the citizens within one week after the test is received at the laboratory. Citizens with a negative test result are referred to the next screening round (two-year interval) and citizens with a positive test result receive an appointment for colonoscopy. Non-participating citizens are automatically referred to the next screening round.

Danish residents are obliged to order a digital signature which is used to log in to a secure national e-mail platform, where all mandatory digital communication with Danish authorities (including hospitals) takes place via the unique civil registration number. Some citizens (8.7% of the population aged 45–74 years during the summer of 2017 [28]) can be exempted from digital communication [29] and receive conventional mail via a remote printing system, in which an external supplier prints out and sends all letters to exempted citizens.

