**Fig. 1 Fig1:**
[figure not shown]
Participant *flow chart*. Figure depicting the data collection, interventions, and participant flow in the trial

The intervention and control groups receive the baseline questionnaire before the screening invitation. This might increase screening awareness and possibly screening uptake and knowledge in these groups – a true Hawthorne effect. To be able to assess the effect of the questionnaire, a historic cohort will be introduced as in other decision aid trials [30]. This group will receive their questionnaire after screening invitation and uptake assessment.

This study entails evaluating the offer to use the decision aid. Even though participants may not necessarily use it, not using the decision aid is not a specific issue in this study as it is a pragmatic evaluation of offering it in a routine screening program.

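### The historic cohort's 50–74 age range takes in citizens aged 50–52, whom the programme's own rules place outside the stated January–March 2017 invitation window and who have no counterpart in the 53–74 trial sample

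*Protocol article*

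**What the plan says.** **Samples.** Study population defines the trial sample as "a random sample of 10,000 53–74-year-old citizens, born in December, and resident in the Central Denmark region on 1 August 2017" and the historic sample as "a random sample of 5000 50–74-year-old citizens, born in October, and resident in the Central Denmark Region on 1 August 2017", the latter "invited for screening during January–March 2017) for the historic study arm". The abstract gives 50–74 for both; for the trial arms it reads "two-arm randomized controlled trial among 10,000 50–74-year-old citizens".

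**Invitation rules.** Setting describes a four-year prevalence round from 2014 with one invitation per citizen, ordered by birth month. It adds: "Citizens turning 50 or 75 years during the prevalence round are invited just before their birthday if not invited earlier". Biennial invitations start in 2018.

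**Purpose and timing of the cohort.** Study design gives the purpose: "To be able to assess the effect of the questionnaire, a historic cohort will be introduced". Its single questionnaire follows invitation by 6–9 months (abstract) or 6–8 months (Study processes).

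**Contrasts.** Table 1 lists three-way comparisons of arm 1, arm 2 and the cohort (H). Its directional hypotheses involving H are arm 1 above H for knowledge and uptake, and arm 1 below H for decisional conflict. Statistical methods uses arm 2 as the reference for both arm 1 and H. Table 1 also has a baseline worry row that includes H.

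**The concern.** The cohort's stated task is to show what the baseline questionnaire does by itself. That needs a group like arm 2 in everything except the questionnaire. An age band that arm 2 cannot contain, invited in other years, weakens this likeness. The questionnaire outcomes would also be collected at a much longer distance from the screening decision than in the rest of the cohort, and knowledge and decisional conflict depend on that distance.

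The second issue is interpretation. Arm 1 differs from H by the decision aid and by the baseline questionnaire, so a difference between them cannot be credited to the decision aid alone. If Table 1 is used as the list of hypotheses to report, the contrast that answers the cohort's own question has no entry in the hypothesis column.

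**Working it through.** **1. Reproduce the plan's own lower limit for the trial arms.** Inputs: round starting in 2014 (Setting), December births, age taken on 1 August 2017. The article attaches that date to residence; applying it to age is an assumption.

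- Age 53, born December 1963: turned 50 in December 2013, before the round, so invited by birth month.
- Age 52, born December 1964: turned 50 in December 2014, inside the round, so invited around that birthday.

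The youngest December-born age not yet invited is 53, which is the limit that Study population sets for the trial arms.

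**2. The same arithmetic for October births.**

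- Age 50: born October 1966, turned 50 in October 2016.
- Age 51: born October 1965, turned 50 in October 2015.
- Age 52: born October 1964, turned 50 in October 2014.
- Age 53: born October 1963, turned 50 in October 2013, before the round.

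The first three fall inside the round. The clause on earlier invitation can only move their date further back, and there is no second invitation before 2018, so none of them belongs in January–March 2017. Taking age in mid-February 2017 gives the same birth years. Taking it at the end of 2017 still leaves ages 50–52 outside the window, with birthdays in October 2017, 2016 and 2015.

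**3. Delay to the questionnaire.** Invitation in January–March 2017 plus 6–9 months, with residence fixed on 1 August 2017, puts the questionnaire at about August–December 2017. Counted from the 50th birthday, the delay is:

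- October 2016: 10–14 months.
- October 2015: 22–26 months.
- October 2014: 34–38 months.

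This is roughly 1 to 3 years, against 6–9 months as stated.

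**4. Size.** Ages 50–74 span 25 year-groups, so with equal groups (assumption) the share is 3/25 = 12%, and 0.12 × 5000 = 600 sampled citizens. A share of 10–15% gives 500–750.

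With the rates in Power calculations (47% without a sample by day 45, 26% lower educational attainment, 50% response):

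- Analysable: 5000 × 0.47 × 0.26 × 0.50 = 305.5, about 306.
- Aged 50–52: 0.12 × 305.5 = 36.7, about 37.
- Remaining: 305.5 − 36.7 = 268.8, about 269 (260–275 for shares of 15% to 10%).

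If the 45-day exclusion does not apply to H: 5000 × 0.26 × 0.50 = 650, of whom 78 are aged 50–52, leaving 572. These counts assume that response and educational attainment do not vary with age.

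**5. Effect on an H estimate.** Shift = share × difference between ages 50–52 and the rest. The documents give no such difference. For assumed differences of 5, 10 and 20 percentage points, the shift is 0.6, 1.2 and 2.4 points.

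**6. The contrasts.** (Arm 1 − H) = (arm 1 − arm 2) + (arm 2 − H). The first term is the randomized effect of offering the decision aid. The second carries the questionnaire effect, together with any difference between the non-randomized groups. Table 1's directional entries for H give the sum; Study design and Statistical methods call for the second term.

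**7. Worry row.** Questionnaires and Study processes give H one questionnaire, after screening. It contains worry items, but not at a time that corresponds to the trial arms' baseline.

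**The case against.** The strongest reply is that the abstract describes the cohort as people invited early in 2017. Read as an eligibility condition, this already excludes ages 50–52, and invitation dates exist in the programme database. That is a workable route. But Study population draws the sample from the Civil Registration System by age, birth month and residence, and the resulting lists hold only the civil registration number, name and address. The window appears there as a description of the sample, and no step removes those outside it.

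It is also fair to say that the affected part is small, that the comparison is ancillary, and that arm 1 versus H is a legitimate description of aid plus questionnaire against unprompted care. All of that stands.

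A reader might infer more than the documents support:

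- **That arm 2 versus H is missing.** It is not. Statistical methods uses arm 2 as the reference for H in the uptake, linear and ordinal regressions, and Table 1's comparison column covers it. Only the hypothesis column is out of step.
- **That the lack of stated covariate adjustment is a fault.** Adjustment sets are commonly left to a statistical analysis plan, which is not at hand.
- **That longer recall distorts uptake.** Uptake comes from the programme database at 90 days after invitation.
- **That 600 unsuitable people enter the analysis.** The 600 are sampled; about 37 would be analysable under the rates above.
- **That H should leave the worry row.** This would delete Table 1's only worry comparison with H. The time point is what needs correcting.

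**Conclusion.** The age contradiction holds and follows from the article's own calendar. The 53-year limit was set for the trial sample and not for the historic sample, and the abstract's 50–74 for the trial arms disagrees with Study population.

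About 12% of the historic sample is affected, assuming equal year-groups. The consequence is some bias, of unknown direction and probably modest size, in arm 2 versus H: for questionnaire outcomes through age mix and delay, for uptake through age mix and year of invitation only. Randomized arm 1 versus arm 2 is not touched.

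The Table 1 part is a mismatch of wording between the hypotheses and the cohort's purpose and planned regressions. It matters mainly because it invites a wrong attribution of an arm 1 versus H difference.

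**What to change.** 1. Draw the historic sample at ages 53–74, or state that it is restricted to citizens whose recorded invitation date lies in January–March 2017. Align the abstract's age range for both samples.
2. In Table 1, enter arm 2 versus H as the questionnaire-effect contrast for knowledge, uptake and decisional conflict. If arm 1 versus H is kept, state that it combines the decision aid and the questionnaire and is not attributed to the decision aid alone.
3. In the worry row, show that the value for H comes from its single questionnaire after screening.

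The cost is one sampling criterion and a few table entries. With births spread evenly over the year (assumption), the region's roughly 395,000 residents aged 50–74 give 395,000 / 12 ≈ 32,900 per birth month, of whom 22/25, or about 29,000, are aged 53–74. A sample of 5000 can therefore be drawn without loss. If the sample is already drawn and the 50–52 group is dropped, about 269 analysable respondents remain under the 45-day exclusion, still above the 200 per group in Power calculations. That 200 is reproduced for 43% versus 57% (two-sided 5%, 80% power); the underlying proportions are not given in the article.

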### Outcomes

The outcomes assessed in this trial are presented in Table 1.

**Table 1 Tab1:** Trial outcomes

Outcome	Characteristics	Assessment time	Comparisons^a^	Null Hypothesis^a^
Primary outcome (Informed choice elements)				
Knowledge	Numeric scale	Baseline	1 vs. 2	No difference
	Numeric scale	Dif_Follow-up-baseline_^b^	1 vs. 2	1 > 2
	Numeric scale	Follow-up	1 vs. 2 vs H	1 > 2 and 1 > H
Attitudes	Numeric scale	Baseline	1 vs. 2	No difference
	Numeric scale	Dif_Follow-up-baseline_^b^	1 vs. 2	No difference
Uptake	Dichotomous	Follow-up	1 vs. 2 vs H	1 > 2 and 1 > H
Secondary outcomes				
Decisional conflict	Numeric scale	Follow-up	1 vs. 2 vs H	1 < 2 and 1 < H
Worry	Numeric scale	Baseline	1 vs. 2 vs H	No difference
	Numeric scale	Dif_Follow-up-Baseline_^b^	1 vs 2	1 < 2
Effect modifiers and confounders				
Health literacy	Numeric scale	Baseline	1 vs. 2 vs. H	No difference
Background data				
Family income	Categorical	Post survey	1 vs. 2 vs. H	No difference
Occupation	Categorical	Post survey	1 vs. 2 vs. H	No difference
Marital status	Dichotomous	Post survey	1 vs. 2 vs. H	No difference
Ethnicity	Categorical	Post survey	1 vs. 2 vs. H	No difference

*H* historic study arm

^a^Group 1 refers to the intervention group and group 2 refers to the control group

^b^Dif_Follow-up-Baseline_: The mean increase or decrease in knowledge, attitude, and worry-score from baseline to follow-up will be estimated. Means will be compared between the two study arms

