#### Study processes

Seven to 20 weeks before the invitation date, the included citizens in study arms 1 and 2 will receive a link to the baseline questionnaire via their digital mail (with remote printing for exempted citizens). Questionnaire reminders will be sent out after two weeks. Instead of a second questionnaire reminder, non-respondents will be contacted via telephone after four weeks and invited to fill out the questionnaire via telephone interview. In a pilot study, the response rates among lower educational attainment and medium/higher educational attainment citizens using an invitation and a two-week reminder were assessed at 27% and 55%, respectively. The response rates increased to 40% and 64%, respectively, in the two groups, by using telephone interviews. Accordingly, we expect telephone interviews to help reach more of the lower educational attainment citizens. Questionnaire respondents will also be asked for consent to the obtaining and analysis of screening data (date of invitation, reminder, receipt of test in laboratory, and test result) from the screening program database.

Citizens who respond to the questionnaire and give consent to the use of registry data will be randomly allocated into study arms 1 and 2. Allocation will be performed in the ratio 1:1 and will use a computer-generated algorithm for randomization, based on a simple randomization procedure. Randomization will be conducted based on the study participants’ record-ID numbers. Participants will not be able to change study arm after allocation and there will be no blinding.

Citizens who take up screening within 45 days after the screening invitation and citizens with medium or higher educational attainment (i.e. 10 years or more of education) will be excluded from the analyses after randomization. This might cause attrition bias. However, randomization will be conducted externally before screening uptake is known. Furthermore, educational attainment will not be available to researchers at an individual level, unless data are pseudonymized. However, educational level and screening uptake within 45 days of invitation is not expected to be associated with study arm and, hence, no attrition bias is expected.

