### Statistical methods

All statistical analyses will be carried out in Stata/SE 14 (STATACorp LP, College Station, TX, USA). Analyses will be carried out on a 5% significance level, stratified to gender. Estimates will be presented with 95% confidence intervals. Intention-to-treat analyses will be conducted.

Pearson’s chi-square test will be used to test differences in demographic characteristics between respondents and non-respondents as well as between those included in each study arm with lower educational attainment, in order to test for baseline differences. Furthermore, differences in educational attainment and screening uptake within 45 days in each study arm will be compared in order to evaluate the risk of attrition bias.

The main outcome of the trial is informed choice. Informed choice is difficult to measure and the evaluation will be based on adequate knowledge about CRC screening and consistency between attitudes towards CRC screening and screening uptake. This will be judged at group level not individual level. [46] Differences in distributions of responses to knowledge, attitudes, uptake, decisional conflict, and worries in the study arms will be analyzed using the independent sample t-test for continuous variables and Pearson’s chi-square test for categorical variables. The relative risk (RR) will be estimated for uptake using a logistic regression analysis with study arm 2 as the reference comparing to both study arm 1 and the historic cohort. Citizens are defined as having taken up CRC screening if they returned a stool sample within three months after the screening invitation was sent out [47]. For the numeric scale outcomes, a linear regression analysis will be conducted to compare the means between study arms 1 and 2 and study arm 2 and the historic cohort, using study arm 2 as the reference. For ordinal scales, not normally distributed as assessed by histograms and qq-plots, ordinal regression analyses will be conducted, estimating odds ratios for higher scores in study arm 1 and the historic cohort as compared to study arm 2, using study arm 2 as the reference.

Further, generalized linear models from the binary family will be conducted to test if socioeconomic variables (including health literacy) modify the effectiveness of the decision aid on knowledge, attitudes, and uptake. *P* values for these analyses will be estimated using the Wald test.

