### Power calculations

The smallest difference between outcomes between groups is expected to be found in attitudes estimates (a 14% difference in proportions having a positive attitude towards screening [19]) Based on this assumption, power calculations (considering a 5% significance level and an 80% statistical power) indicate that we need to include 200 citizens with lower educational attainment in each group. We expect 47% of citizens invited to CRC screening not to return a stool sample within 45 days. Further, we know that 26% of the population has lower educational attainment [49]. By combining mailed invitations and reminders with telephone calls, we aim to reach a response rate of at least 60% for baseline questionnaire and 80% for follow-up (i.e. study participants). Further, we expect a 50% response rate in the historic study arm. In order to be able to make gender stratified analyses, and considering the rate of screening reminder, rate of lower educational attainment, and questionnaire response rate, we need to include 5000 citizens in each study arm.

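### Arms 1 and 2 are compared on change scores, and for knowledge also on follow-up scores, with no baseline covariate named; baseline-adjusted regression is more precise and would give knowledge one primary test

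*Protocol article*

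**What the plan says.** Table 1 of the protocol article (Outcomes) lists a follow-up-minus-baseline row, arm 1 versus arm 2, for knowledge, attitudes and worry. Footnote b explains: "The mean increase or decrease in knowledge, attitude, and worry-score from baseline to follow-up will be estimated", with means then compared between the two arms. Knowledge has a further row, the follow-up score in arm 1 versus arm 2 versus the historic cohort. The Primary outcome section also names both the level and the change for knowledge. Neither is put first.

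Statistical methods says that differences in responses "will be analyzed using the independent sample t-test for continuous variables". It then describes a linear regression comparing means with arm 2 as the reference. Study arm is the only term named. The section adds a switch: "For ordinal scales, not normally distributed as assessed by histograms and qq-plots, ordinal regression analyses will be conducted". Analyses are to be stratified by gender.

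On the available data, Study processes states that "Citizens who respond to the questionnaire and give consent to the use of registry data will be randomly allocated" to the two arms. The Questionnaires section lists knowledge, attitudes and worry in the baseline questionnaire. The historic cohort gets one questionnaire only, months after its screening invitation.

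**The concern.** Each scale is measured before and after the intervention in both randomized arms, yet neither planned contrast makes the best use of the first measurement. A change score subtracts the whole baseline value, which adds noise when the correlation between the two measurements is modest. A comparison of follow-up means leaves the baseline out.

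Two things are at stake. The first is precision, in a trial whose analysed groups are small once early screeners, the better educated and non-respondents are removed, and which also plans analyses by gender. The second is that the primary knowledge result for arm 1 versus arm 2 comes in two unranked versions. Their estimates differ by exactly the observed baseline difference, so one can be significant and the other not.

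**Working it through.** **Inputs from the article.** Power calculations gives "considering a 5% significance level and an 80% statistical power" and "a 14% difference in proportions having a positive attitude towards screening", and concludes that "we need to include 200 citizens with lower educational attainment in each group". It also gives 5000 citizens per arm, 60% baseline response, 80% follow-up response, 47% with no sample by day 45, and 26% with lower education. Study processes says: "Allocation will be performed in the ratio 1:1".

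**Assumed, not in the article.** Two-sided tests, equal standard deviations (SDs) at baseline and follow-up, and a correlation ρ between them of 0.3, 0.5 or 0.7.

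**1. The plan's own figure.** The base proportion is not stated. Comparing two proportions 14 points apart, two-sided 5%, 80% power, gives 200 per group for 43% versus 57% and 196 for 50% versus 64%, both without continuity correction. The stated 200 is reproduced for proportions near one half. It concerns a proportion, so it does not size the mean-score comparisons directly.

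**2. Expected analysed number.** 5000 × 0.60 × 0.80 × 0.47 × 0.26 = 293 per arm, or about 147 per gender if split evenly. With the pilot's 40% response among lower-educated citizens in place of 60%, 5000 × 0.40 × 0.80 × 0.47 × 0.26 = 195.5.

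**3. Variance per person, in units of the follow-up variance.** Follow-up mean: 1. Change score: 2(1 − ρ). Baseline-adjusted regression: 1 − ρ². The ratio of adjusted to change score is (1 − ρ²) / [2(1 − ρ)] = (1 + ρ)/2.

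| ρ | Change score | Adjusted | Adjusted ÷ change score | Adjusted ÷ follow-up mean |
|---|---|---|---|---|
| 0.3 | 1.40 | 0.91 | 0.65 | 0.91 |
| 0.5 | 1.00 | 0.75 | 0.75 | 0.75 |
| 0.7 | 0.60 | 0.51 | 0.85 | 0.51 |

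For every ρ strictly between 0 and 1 the adjusted analysis has the smallest variance. Below 0.5 the change score is less precise than ignoring the baseline.

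**4. In numbers of citizens.** The precision of 200 per arm analysed by change score is reached by adjusted regression with 200 × 0.65 = 130, 200 × 0.75 = 150 or 200 × 0.85 = 170 per arm.

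**5. In power.** With 200 per arm, follow-up means have 80% power for a difference of (1.96 + 0.84) × √(2/200) = 0.28 SD. For that difference, at ρ = 0.3 / 0.5 / 0.7, power is 66% / 80% / 95% by change score and 84% / 90% / 98% by adjusted regression.

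**6. Two knowledge tests.** Under no effect, the two test statistics have correlation √((1 − ρ)/2): 0.592, 0.500 and 0.387. Simulation with each tested at 5% gives a chance of at least one false positive of 8.8%, 9.1% and 9.3%, against 5% for a single test.

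**The case against.** The strongest reply is that this is a matter of efficiency, not error. Arms are randomized, so a difference in mean change estimates the arm effect without bias and keeps its type I error. That stands. A reader might infer from the talk of subtracting too much baseline that change scores bias the result; the documents give no ground for that.

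A second reply is that covariate lists often sit in an analysis plan that is not shown, and that the article never calls its regression unadjusted. This holds for the regression sentence. It does not remove the point, because footnote b itself fixes the change-score contrast and the article itself lists two knowledge tests.

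Third, the scope is limited. In Table 1 only knowledge has both a change row and a follow-up row, so it would be wrong to say that all three scales are tested twice there. Nor can an adjusted model replace every planned knowledge comparison: the historic cohort has no pre-invitation baseline, and follow-up levels are still needed for that contrast and for judging adequate knowledge at group level.

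Fourth, the switch to ordinal regression could be read as an unplanned choice. It is not: the criterion is written down, and nothing says that it is applied after looking at the arms separately. It remains a visual judgement that would change the effect measure from a mean difference to an odds ratio, which is reason enough to name one main model.

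Finally, baseline scores exist for all randomized citizens at questionnaire level. Missing knowledge items are scored as wrong, so that score always exists, but single attitude or worry items may be missing.

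**Conclusion.** The point holds as a worthwhile improvement, not as a flaw that invalidates the trial. The planned arm 1 versus arm 2 analyses are valid but give away precision: 15% to 35% of the change-score variance and 9% to 49% of the follow-up-mean variance over correlations of 0.3 to 0.7. These figures rest on an assumed correlation and on equal SDs, neither of which the article states; the direction holds for any correlation strictly between 0 and 1 when the SDs are equal. The roughly 9% false-positive chance applies to the two arm 1 versus arm 2 knowledge tests if success on either counts, and the article does not say which would count.

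It should not be read as a claim that the trial is too small overall. On the article's own rates, 293 per arm exceeds the stated 200. The lost precision matters most within gender, at about 147 per arm, or if response is nearer the pilot's.

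**What to change.** - For arm 1 versus arm 2, regress the follow-up score on study arm and the same scale's baseline score, with robust standard errors, fixed in advance.
- Make this the single primary arm 1 versus arm 2 test for knowledge, and the main analysis for attitudes and worry.
- Run it within each gender for the planned stratified analyses, and add gender as a covariate in any pooled analysis.
- Keep change scores as description and ordinal regression as a sensitivity analysis.
- Keep the comparison with the historic cohort as an unadjusted follow-up comparison.

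The cost is a change of wording in Table 1 and Statistical methods, or in the analysis plan, including a sentence on how gender is handled. The baseline scores are already collected, and neither the design nor the sample changes.
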